### Data management

Clinical data will be collected locally via Research Electronic Data Capture (REDCap), an Internet-based electronic case report form (CRF). The research coordinator at each hospital will provide training in study procedures to improve adherence to the protocol. Furthermore, they will check CRFs and contact responsible staff members to ensure data quality.

### Statistical methods

The primary endpoint will be analyzed based on an intention-to-treat principle, regardless of whether they completed the originally allocated treatment study protocol. Any reasons for protocol violations will be described. All *p* values are two-tailed, and the significance level will be a *p* value <0.05.

Continuous variables will be expressed as means and standard deviations (normal distribution) or median with interquartile range (skewed distribution). Student’s *t* test (normal distribution) or Mann-Whitney *U* test (skewed distribution) will be used for group comparisons. Data will be presented as frequencies and percentages for categorical variables. Categorical variables will be compared using Pearson’s chi-squared test or Fisher’s exact test as appropriate. Time-dependent data will be presented as Kaplan-Meier curves. Statistical uncertainty will be expressed in terms of a relative risk and 95% confidence intervals.

Data will be analyzed using the statistical program SPSS version 20.0 for Windows (SPSS Inc., Chicago, IL, USA).

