**Discussion:**

The Bi-TPAI trial will prove that intensive insulin therapy is non-inferior to plasmapheresis. Intensive insulin therapy should be an effective, safe, available, and cheaper triglyceride-lowering therapy for hypertriglyceridemia-induced acute pancreatitis.

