## Methods

### Trial design and setting

The Bi-TPAI trial is a national, multicenter, parallel group, open, non-inferiority, randomized controlled trial that will include 220 patients with HTG-AP, from 17 large tertiary hospitals in China. The Bi-TPAI trial will be conducted according to the principles of the Declaration of Helsinki [10]. The Institutional Review Board of Peking Union Medical College Hospital, Chinese Academy of Medical Sciences & Peking Union Medical College in Beijing, China, approved the trial protocol (version 2.0, reference number ZS-1340, date 20 June 2017). The schedule of enrolment, intervention and assessments following the Standard Protocol Items: Recommendation for Interventional Trials (SPIRIT) guidelines (Additional file 1) is presented in Fig. 1.

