### Study endpoints

The primary endpoint is the time it takes for tTG to drop to 500 mg/dl. The secondary endpoints are (1) ICU and hospital length of stay (LOS); (2) 28-day mortality; (3) severity of HTG-AP - this will be reported according to the revised Atlanta criteria [11], the Acute Physiology and Chronic Health Evaluation II (APACHE II) score, the Ranson score and computed tomography (CT) grading; (4) incidence of hypoglycemia; (5) HTG-AP complications according to the revised Atlanta criteria [11]; and (8) cost-effectiveness.

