### Sample size calculation

The Bi-TPAI trial is a non-inferiority randomized controlled trial. Respective studies and series reported 60–72% of cases with TG < 5.6 mmol/l after one or two sessions of plasmapheresis [4, 12]. A total of 176 participants (88 per group) is required to show non-inferiority of intensive insulin therapy compared to plasmapheresis therapy, with a two-sided significance level of 5% and statistical power of 80%. To account for drop-out and missing data, the sample size is increased by 20% to a final sample size of 220 participates (110 per group).

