## Discussion

As hypertriglyceridemia may cause more severe acute pancreatitis and worse symptoms, it is imperative to resolve the underlying etiology. There are many available therapies for hypertriglyceridemia-induced acute pancreatitis, including oral lipid-lowering agents, intravenous insulin with or without heparin, and plasmapheresis [13]. Effectiveness, side effects, cost, and availability may influence the final choice of therapy.

Several studies have reported on the effectiveness and safety of insulin [14, 15]. A retrospective cohort study in 2016 showed a significant TG decrease at each time interval in patients treated with intravenous insulin and plasmapheresis, but no difference in clearance rate or length of stay between intravenous insulin and plasmapheresis [16].

A prospective randomized controlled trial (RCT) showed the superiority of high-volume hemofiltration (HVHF) over insulin combined with heparin in lowering TG levels. However, as He, et al. demonstrated in 2016, early HVHF cannot improve clinical outcomes [17]. As for heparin, the effects of heparin on triglycerides are transient because of increased transport of LPL to the liver for degradation [18].

Plasmapheresis is relatively expensive and labor intensive and is associated with complications. Intensive insulin therapy costs much less than plasmapheresis. Researchers calculated that the direct cost to a hospital would be around US$36, if a patient requires 120 units of regular insulin within 24 h. However, a 24-h plasmapheresis course would cost US$3800 plus the variable cost of associated blood products. There is at least 100-fold cost difference between the two therapies [16].

At present, no studies have been conducted to identify the best route (intravenous or subcutaneous) for insulin treatment or the best dose to administer insulin in order to treat HTG-AP. The Bi-TPAI trial plans to include 220 patients from multiple hospitals and should provide adequate power to answer the question of whether intensive intravenous insulin therapy significantly lowers serum TG similarly to plasmapheresis.

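### The trial is declared and sized as non-inferiority, but no margin is stated and the only inferential criterion is two-tailed p<0.05 from tests of no difference, which cannot establish non-inferiority

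*Protocol article*

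**What the plan says.** The article commits to non-inferiority in several places:

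- Trial design and setting describes a "multicenter, parallel group, open, non-inferiority, randomized controlled trial".
- Sample size calculation opens with "The Bi-TPAI trial is a non-inferiority randomized controlled trial" and says that a total of 176, or 88 per group, "is required to show non-inferiority of intensive insulin therapy compared to plasmapheresis therapy". The error rate assumed there is 5% two-sided and the power 80%. The total is then raised to 220 for drop-out and missing data.
- The abstract's Discussion states: "The Bi-TPAI trial will prove that intensive insulin therapy is non-inferior to plasmapheresis".
- The main Discussion puts the question as "whether intensive intravenous insulin therapy significantly lowers serum TG similarly to plasmapheresis".

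The endpoint is a time. Study endpoints says: "The primary endpoint is the time it takes for tTG to drop to 500 mg/dl".

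Statistical methods says of all p "values are two-tailed, and the significance level will be a" p value below 0.05. It names the t test or Mann-Whitney test for continuous variables and chi-squared or Fisher's exact test for categorical ones. It also mentions Kaplan-Meier curves for time-dependent data, and a relative risk with 95% confidence intervals to express uncertainty. No section gives a margin, and no interval bound is compared with one.

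**The concern.** A non-inferiority claim requires rejecting the hypothesis that insulin is worse than plasmapheresis by at least the margin. The named tests reject a different hypothesis, that of no difference. A significant result in favour of insulin would support a stronger claim, and a significant result against it would count against insulin. In every other case the stated criterion yields a non-significant p value, which does not show that a clinically important deficit has been excluded.

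The primary conclusion is at stake. If a non-significant result were taken as similarity, the chance of wrongly accepting an inferior treatment would not be controlled. That chance would also rise as the number of analysable patients falls, so drop-out and noisy data would make the claim easier to reach.

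**Working it through.** **Inputs from the article.** Sample size calculation gives 88 per group (176), two-sided 5%, 80% power, 60–72% of plasmapheresis cases at target after one or two sessions, and a 20% allowance. Randomization is 1:1. The margin, the assumed insulin-arm rate and any assumption on the time scale are not given.

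**Drop-out step.** 176 / (1 − 0.20) = 220. This reproduces.

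**Can 88 per group be reproduced?** Not from the stated inputs, because the margin is absent. It can only be solved backwards. Assume equal true rates p in both arms, one-sided 0.025 and 80% power:

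n per arm = 2p(1 − p)(1.960 + 0.842)² / margin², where (1.960 + 0.842)² ≈ 7.849.

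With p = 0.66 (midpoint of 60–72%) and a 20-point margin: 2 × 0.66 × 0.34 × 7.849 / 0.04 = 88.06. Solving for the margin at n = 88:

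| Assumed rate in both arms | Implied margin |
|---|---|
| 60% | 20.7 points |
| 66% | 20.0 points |
| 72% | 19.0 points |

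At one-sided 0.05 the implied margin would be about 17–18 points.

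**Is 88 a superiority calculation on 60% versus 72%?** No. (1.960 × √(2 × 0.66 × 0.34) + 0.842 × √(0.60 × 0.40 + 0.72 × 0.28))² / 0.12² ≈ 244 per arm.

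**Time scale.** With one event per patient (176 events), 88 per arm would correspond to a hazard-ratio margin of exp(2.802 / √(176/4)) = exp(0.422) ≈ 1.53. Treated as a mean time, it would correspond to 2.802 × √(2/88) ≈ 0.42 SD. The article states neither.

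**Error rate at the implied margin.** Assume control 66%, insulin 46% and a margin of 20 points, so that insulin is exactly at the unacceptable boundary. The chi-squared test is non-significant when the absolute difference is below 1.96 × s₀, with s₀ = √(2 × 0.56 × 0.44 / n). The true standard error is s₁ = √((0.66 × 0.34 + 0.46 × 0.54) / n).

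- n = 88: s₀ = 0.0748, s₁ = 0.0733; (1.96 × 0.0748 − 0.20) / 0.0733 = −0.73, so the probability is about 0.23. Exact binomial enumeration gives 0.217.
- n = 110: s₀ = 0.0669, s₁ = 0.0656; the ratio is −1.05, so the probability is about 0.147. Exact enumeration gives 0.149.
- A rule requiring the lower bound of the two-sided 95% interval for the difference to lie above −20 points has a nominal error of 2.5%. By exact enumeration with an unpooled interval it is 2.2% at 88 and 2.3% at 110.

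For control rates from 60% to 72%, still with a 20-point deficit, the exact non-significance rates are 21–23% at 88 per arm and 13–15% at 110.

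**If the justified margin is tighter.** On the same response-rate scale, with equal rates of 60–72%, a 15-point margin needs 141–168 per arm and a 10-point margin 317–377. At p = 0.66 and 15 points, power is Φ(0.15 / √(0.4488/n) − 1.96): Φ(0.14) ≈ 56% at 88 and Φ(0.39) ≈ 65% at 110.

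**The case against.** Several points on the other side have force.

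- **The article never says that a non-significant p value will be read as non-inferiority.** This is correct. A reader might infer it because the stated criterion offers no other route to similarity short of superiority, but the text does not say so. The point therefore rests on what the stated analysis can establish.
- **A two-sided 5% level is not an error.** This stands. It matches a two-sided 95% interval, which is a valid non-inferiority tool, and it agrees with the sample size section. The fault is that no interval bound is set against a margin.
- **No test is expressly assigned to the primary endpoint.** This also stands. The tests are listed by type of variable, and time-dependent data are given Kaplan-Meier curves. One cannot say that a superiority test is prescribed as the primary non-inferiority test, only that no criterion suited to non-inferiority is given. The relative risk with its interval does not fill the gap, because it is tied to no margin and does not fit a time endpoint.
- **The full protocol or an analysis plan may hold a margin.** It may, so one cannot conclude that the trial has none. However, the article prints both a non-inferiority sample size and an inferential criterion, and the two do not fit each other. That is a fault in the text as it stands.
- **Smaller deficits look more alarming.** A reader might quote the higher non-significance rates for insulin 10 or 15 points worse, or for a hazard ratio of 0.75, as false-claim rates. Measured against the implied margins (about 20 points, or a hazard ratio of about 1/1.53 ≈ 0.65 for reaching target), those deficits are acceptable, so the rates are not errors. Only the 20-point case compares like with like.

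**Conclusion.** The point holds: as written, the analysis cannot support the conclusion for which the trial is designed and sized. No margin is stated on any scale, and the only inferential criterion addresses a null of no difference.

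If a non-significant chi-squared test were taken as non-inferiority, an insulin regimen truly 20 points worse would pass in about 22% of trials at 88 per arm and 15% at 110, against about 2.5% under an interval rule. These figures rest on an assumed 66% control rate, on a margin of 20 points (range 19–21) inferred from the sample size and not documented, and on a response proportion, whereas the endpoint is a time. They show the size of the risk and do not predict how the investigators would report the trial. Because the gap governs the primary conclusion, it must be closed before any unblinded comparison.

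**What to change.** Before any unblinded comparison:

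1. In Sample size calculation and Statistical methods, state the margin on the scale of the primary endpoint (time to TG 500 mg/dl) and justify it clinically. Do not choose it because it reproduces 88 per group.
2. In Statistical methods, name the effect measure for that endpoint and add wording such as: Non-inferiority will be concluded only if the relevant bound of the two-sided 95% confidence interval for insulin versus plasmapheresis excludes the margin; a non-significant difference is not evidence of non-inferiority.
3. Keep two-tailed p values for the secondary endpoints, and for superiority tested after non-inferiority has been shown.
4. Show the sample size from the stated margin and its other assumptions.

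The cost is wording only. It would be wrong to promise that the planned numbers suffice whatever the margin. If the justified margin is tighter than the one 88 per group implies, restate the power that 176 to 220 patients give.

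### The only stated group comparison that fits ICU and hospital length of stay ignores death, so an arm with more early deaths can look better on this secondary endpoint (minor)

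*Protocol article*

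**What the plan says.** Under Study endpoints, the protocol article opens its list of secondary endpoints with "1) ICU and hospital length of stay (LOS); (2) 28-day mortality". They are two separate items, and nothing says how the stay of a patient who dies is counted.

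Under Statistical methods, the summary rule is: "Continuous variables will be expressed as means and standard deviations (normal distribution) or median with interquartile range (skewed distribution"). The comparison rule follows directly: Student's t test for normal data, or the Mann-Whitney U "test (skewed distribution) will be used for group comparisons". Pearson's chi-squared and Fisher's exact test are reserved for categorical variables. One further sentence could reach length of stay: "Time-dependent data will be presented as Kaplan-Meier curves". It concerns display only; it names no test and does not say what happens to deaths.

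Length of stay is not named anywhere in that section. The article gives no expected mortality and no expected stay.

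**The concern.** Death ends a stay. In a t test or Mann-Whitney test on observed days, a patient who dies on day 4 scores better than one who goes home alive on day 14. The scale therefore has no fixed meaning: a short stay is good if it ends in discharge and bad if it ends in death. Deaths are possible in this population, and the trial measures them as an endpoint.

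What is at stake is the between-arm reading of a secondary endpoint. If one arm has more early deaths, its length-of-stay result is pushed in its favour even when survivors in both arms stay equally long. The Discussion cites an earlier cohort's lack of difference in stay when comparing insulin with plasmapheresis, so readers are likely to take this endpoint as a treatment comparison.

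**Working it through.** **Which rule applies.** Three statements in Statistical methods could govern length of stay.

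- Continuous rule (t test or Mann-Whitney): it fits, since stay is measured in days, and it has no provision for death.
- Categorical rule (chi-squared or Fisher): it does not fit.
- Kaplan-Meier sentence: it could be read to cover stay, but it names no comparison. It would not solve the problem either. Counting death as the end of stay keeps the same bias. Censoring at death treats the patient as still able to be discharged and overstates the probability of discharge.

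**Plan figures used.** There is no length-of-stay figure to reproduce. The only input taken from the plan is the arm size: "the sample size is increased by 20% to a final sample size of 220 participates (110 per group"). This checks: 176 / (1 − 0.20) = 220, and 88 / 0.8 = 110.

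**Assumed inputs (none are in the article).** Stay in survivors is log-normal and identical in both arms, with median 12 or 14 days and log-SD 0.6. Time to death is log-normal with median 4 days and log-SD 0.6. Mortality is pA in arm A and pB in arm B, with pA larger.

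**Shift in mean stay.** The mean of a log-normal is median × exp(0.6²/2) = median × 1.197.

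- Survivors: 14 × 1.197 = 16.76 days, or 12 × 1.197 = 14.37 days.
- Deaths: 4 × 1.197 = 4.79 days.
- Shift (arm A shorter) = (pA − pB) × (survivor mean − death mean), which is (pA − pB) × 11.97 for median 14 and (pA − pB) × 9.58 for median 12.

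**Mann-Whitney probability that arm A has the longer stay (median 14).** The chance that a survivor's stay exceeds a dying patient's is Φ[ln(14/4) / (0.6√2)] = Φ(1.476) = 0.930. Scored on observed days, the probability is 0.5 − 0.430 × (pA − pB). With deaths ranked worst it is 0.5 + 0.5 × (pA − pB).

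| Mortality A v B | Mean shift, median 14 | Mean shift, median 12 | Mann-Whitney, observed days (median 14) | Mann-Whitney, deaths worst |
|---|---|---|---|---|
| 3% v 3% | 0 | 0 | 0.500 | 0.500 |
| 5% v 2% | 0.36 d | 0.29 d | 0.487 | 0.515 |
| 8% v 3% | 0.60 d | 0.48 d | 0.479 | 0.525 |
| 12% v 4% | 0.96 d | 0.77 d | 0.466 | 0.540 |

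Ranking deaths worst reverses the direction in every row where mortality differs.

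**Against sampling error (110 per arm, median 14).** The SD of stay in survivors is 16.76 × √(exp(0.36) − 1) = 11.0 days, so the standard error of the mean difference is 11.0 × √(2/110) = 1.5 days. The standard error of the Mann-Whitney probability is √[221 / (12 × 110 × 110)] = 0.039. At 12% v 4% the shift is 0.96/1.49 = 0.64 standard errors for the mean and 0.034/0.039 = 0.88 for the Mann-Whitney probability. All the rows stay below one standard error.

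**Effect on the test (simulation, 3000 trials, median 12, two-sided 5%).** Share of trials in which each arm has the significantly shorter stay, against a nominal 2.5% each:

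| Mortality A v B | Favours A | Favours B |
|---|---|---|
| 3% v 3% | 2.4% | 2.8% |
| 5% v 2% | 4.6% | 0.8% |
| 10% v 5% | 7.2% | 0.4% |
| 15% v 5% | 17.1% | 0.2% |
| 20% v 5% | 34.7% | 0.1% |

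The distortion becomes material only with a large imbalance.

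**Timing matters.** The shift formula changes sign if patients who die do so after a longer stay than survivors have. The stated direction therefore depends on early deaths.

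**The case against.** The strongest reply is that the article does not say what the concern needs it to say. Length of stay is not named in Statistical methods, no sentence says that deaths enter at observed days, and a Mann-Whitney test with deaths ranked worst would be consistent with the text. A condensed article may leave such coding to the full protocol or analysis plan. This stands in part: it is an inference that observed days will be compared, and it should be worded as one. It does not remove the point. The article fixes a comparison rule for continuous variables without exception, no other named test fits, and the rule taken at face value handles death badly.

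Second, the effect is small and rests on assumed inputs. That stands, and it sets the severity.

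Third, 28-day mortality is reported in its own right, so a difference in deaths would be seen. That stands too. A reader might infer that the rule would hide a harm; the separate mortality endpoint makes that too strong. What remains is that the length-of-stay p value would itself be hard to interpret.

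A reader might also infer that the bias carries into the cost-effectiveness result. The article does not support this. It never says that length of stay feeds that endpoint, and the costs it discusses are those of insulin and plasmapheresis. Bed days actually used are in any case the right cost input, including for patients who die.

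**Conclusion.** The point holds as a minor one. The only stated comparison that fits ICU and hospital stay does not account for death. Used on observed days, it can favour the arm with more deaths, provided that mortality differs and deaths are early. On the assumed inputs the apparent advantage is about 0.3 to 0.4 days at 5% v 2% and about 0.8 to 1 day at 12% v 4%. It is zero when the frequency and timing of death are the same in both arms. These sizes depend wholly on assumed survivor stays (median 12 or 14 days) and assumed deaths at a median of 4 days.

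It would go too far to say that the arm with more deaths will look better. The article gives neither the number nor the timing of deaths, and late deaths would act the other way. The primary endpoint, time for triglycerides to fall to 500 mg/dl, is unaffected.

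**What to change.** Add one sentence to Statistical methods that takes ICU and hospital length of stay out of the general continuous rule. Either of these would do:

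- analyse time to discharge alive (from ICU and from hospital), with death as a competing event and cumulative incidence curves by arm; or
- keep the Mann-Whitney test, with patients who die given the worst rank.

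Report the result beside 28-day mortality. Give stay in survivors as description only, because survivors are no longer a randomised comparison, and keep raw bed days for description or as a cost input.

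The cost is one sentence and a little analysis work; sample size and trial conduct do not change. The analysis needs dates of discharge and death. The article does not list these as collected items, but length of stay and 28-day mortality could hardly be derived without them; the sponsor should confirm that they are recorded. The small downside is that the result is less direct to read than a difference in days.

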## Discussion

As hypertriglyceridemia may cause more severe acute pancreatitis and worse symptoms, it is imperative to resolve the underlying etiology. There are many available therapies for hypertriglyceridemia-induced acute pancreatitis, including oral lipid-lowering agents, intravenous insulin with or without heparin, and plasmapheresis [13]. Effectiveness, side effects, cost, and availability may influence the final choice of therapy.

Several studies have reported on the effectiveness and safety of insulin [14, 15]. A retrospective cohort study in 2016 showed a significant TG decrease at each time interval in patients treated with intravenous insulin and plasmapheresis, but no difference in clearance rate or length of stay between intravenous insulin and plasmapheresis [16].

A prospective randomized controlled trial (RCT) showed the superiority of high-volume hemofiltration (HVHF) over insulin combined with heparin in lowering TG levels. However, as He, et al. demonstrated in 2016, early HVHF cannot improve clinical outcomes [17]. As for heparin, the effects of heparin on triglycerides are transient because of increased transport of LPL to the liver for degradation [18].

Plasmapheresis is relatively expensive and labor intensive and is associated with complications. Intensive insulin therapy costs much less than plasmapheresis. Researchers calculated that the direct cost to a hospital would be around US$36, if a patient requires 120 units of regular insulin within 24 h. However, a 24-h plasmapheresis course would cost US$3800 plus the variable cost of associated blood products. There is at least 100-fold cost difference between the two therapies [16].

At present, no studies have been conducted to identify the best route (intravenous or subcutaneous) for insulin treatment or the best dose to administer insulin in order to treat HTG-AP. The Bi-TPAI trial plans to include 220 patients from multiple hospitals and should provide adequate power to answer the question of whether intensive intravenous insulin therapy significantly lowers serum TG similarly to plasmapheresis.

One important limitation of the Bi-TPAI trial is that blinding is not possible due to the nature of the intervention. However, attending physicians and nurses who have no specific interest in the trial will be included. Statistical analysis will be performed in a blinded fashion. We hope to answer the question of whether intensive insulin can effectively reduce serum TG and whether this approach is safe and cost-effective.

